## **2.1 PRIMARY OUTCOME**

The primary outcome is imaging-confirmed lower limb DVT with or without symptoms, or PE with symptoms, occurring up to 90 days post-surgery.

## **2.2 SECONDARY OUTCOMES**

Secondary outcomes will be defined as occurring within 90 days of surgery.

- Mortality
- Adverse events related to GCS
- Adherence with GCS\*
- Adherence with EDPTP
- Safety outcome measures

\*Adherence will be assessed in comparison to the advice provided by the local clinical team at the time of discharge i.e., if advised to wear GCS every day for the full duration of extended thromboprophylaxis, then this timepoint will be the level of full compliance for comparison. However, if participants are advised to wear GCS whilst an inpatient only, then this will be used as the level of full compliance.

## **3. STUDY DESIGN**

### **3.1 TYPE OF STUDY**

This is a multi-centre assessor-blinded randomised controlled trial (RCT) consisting of participants undergoing surgical intervention that are deemed to require extended duration thromboprophylaxis with a non-inferiority comparison. Clinicians and participants will be aware of their treatment allocation. Assessors, being those who

perform the lower limb DVT scan and those responsible for collecting follow-up data, will be blinded to the treatment allocation.

Individual participants will be randomised in a 1:1 fashion to one of two thromboprophylaxis strategies:

- EDPTP\* in addition to GCS, or
- EDPTP alone

\*EDPTP includes any anti-thrombotic agent prescribed at a prophylactic dose for prevention of VTE, including low-molecular weight heparin (LMWH), Directly acting Oral AntiCoagulants (DOACs), or antiplatelet therapy.

Randomisation will be electronic with stratification incorporating centre and type of surgery.

The duration of the study will be 39 months including 6-months set up, 24 months of recruitment, 3 months follow-up and 6 months for analysis and dissemination.

The flow diagram summarising the study design can be seen in **Figure 1**.

**Figure 1: Study flow diagram**

[figure not shown]

## **3.2 BLINDING**

Assessors, being those who perform the lower limb DVT scan and those responsible for collecting follow-up data, will be blinded to the treatment allocation. If patients in the GCS arm are still wearing stockings at the time of the scan, they will be instructed to remove them prior to entering the scan room and not inform the scanner of their treatment allocation.

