## **5.3 FOLLOW-UP**

Participants will be contacted by the central study team at days 7, between 21 and 35 days, and 90 days to obtain follow up data. The follow-up will be conducted either by telephone, SMS, web or written depending on participant preference.

Participants will undergo a bilateral full lower limb (groin to ankle) deep venous thrombosis scan at 21- 35 days post-intervention to identify asymptomatic DVT, this is timed to capture the peak onset of events which is at 3 weeks (34). Reasonable travel expenses will be reimbursed for this visit.

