### **Day 7 post procedure**

Day 7 post procedure (data collected via telephone or online survey [link to survey sent via email or SMS])

- VTE outcome (participants will be asked to report on whether or not they have been diagnosed with a DVT or PE within the past 7-days)
- Adverse events associated with GCS will be captured (for those enrolled in the control arm)
- Participant reported adherence to GCS (for those enrolled in the control arm)
- Adherence to EDPTP

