## **Day 90 post procedure**

Day 90 post procedure (data collected via telephone or online survey [link to survey sent via email or SMS])

- VTE outcome (participants will be asked to report on whether or not they have been diagnosed with a DVT or PE since last contact)
- Adverse events associated with GCS will be captured (for those enrolled in the control arm)
- Participant reported adherence (for those enrolled in the control arm)
- Adherence to EDPTP

If the patient reports a VTE within the trial period that was not captured on the 21-to-35-day ultrasound we will request verification that imaging has confirmed the diagnosis.

Mortality within the 90-day follow-up period will also be captured. Follow-up data will be assessed blindly.

As this is a pragmatic trial, we will look to measure adherence and ensure it is reasonable but not attempt to introduce new interventions to increase adherence above what would be reasonably expected. We consulted the patient representatives, who have lived experience of wearing GCS, to establish how best to monitor adherence without unduly promoting increased adherence within the trial. Telephone consultation supplemented with remote messages by smart phone with electronic response to establish adherence was preferred. This was also reflected in wider PPI undertaken for other VTE prevention studies.

Any incidental findings identified during the study from the lower limb VTE ultrasound or self reported follow-up will be reported the clinical care team for any required treatment and follow-up.

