### **8.3. CONFIDENTIALITY**

The Chief Investigator will preserve the confidentiality of participants taking part in the study and is registered under the Data Protection Act.

As follow-ups will be performed by the coordinating centre (Imperial College London), patient identifiable data (name, address, email address and contact telephone number[s]) will be stored on the REDCap database. This identifiable data will only be accessible by researchers at the local site (who will enter the data onto REDCap in the first place) and by the blinded assessors based at the coordinating centre who are responsible for conducting the follow-ups.

The trial manager will only have access to pseudonymised data on REDCap.

The investigator shall permit direct access to subjects' records and source document for the purposes of monitoring, auditing, or inspection by the Sponsor, authorised representatives of the Sponsor and RECs.

Data will be transferred to The University of Edinburgh for the purposes of statistical analysis.

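### Follow-up assessors are declared blinded, yet any contact they administer themselves must put stocking questions to control-arm participants only, so the claim fails for VTE reported at those contacts

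*Protocol*

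**What the plan says.** Section 3.2, repeating section 3.1, extends blinding beyond the scan: "Assessors, being those who perform the lower limb DVT scan and those responsible for collecting follow-up data, will be blinded to the treatment allocation". The day 90 part of section 5.3 adds: "Follow-up data will be assessed blindly".

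Section 5.3 says who makes the contacts: "Participants will be contacted by the central study team at days 7, between 21 and 35 days, and 90 days to obtain follow up data". Section 8.3 shows that these are the people declared blinded. It limits access to identifiable data to local site researchers and to access "by the blinded assessors based at the coordinating centre who are responsible for conducting the follow-ups".

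The content of the contacts depends on the arm. At day 7 the list includes "Adverse events associated with GCS will be captured (for those enrolled in the control arm") and "Participant reported adherence to GCS (for those enrolled in the control arm"). The day 21 to 35 list repeats both items. At day 90 the adverse-event item recurs, with "Participant reported adherence (for those enrolled in the control arm"). Appendix 1 stars the adverse-event and stocking-adherence rows as control arm only. The self-reported VTE question belongs to the same three contacts.

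On mode, section 5.3 says: "The follow-up will be conducted either by telephone, SMS, web or written depending on participant preference". It also records that patient representatives preferred telephone, supplemented by smartphone messages, for establishing adherence.

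**The concern.** A caller who must ask about stockings in one arm and not in the other has to know the arm before asking, and the answers would reveal it anyway. The same contact collects part of the primary outcome from participants who know their own allocation. If knowledge of the arm leads to uneven probing, or to uneven pursuit of imaging confirmation, the groups' event counts can differ for reasons unrelated to treatment. With a 2-point non-inferiority margin, a small deficit of recorded events in the EDPTP-alone arm favours the trial's intended conclusion. Such a bias arises when the data are collected, and the analysis cannot remove it afterwards.

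**Working it through.** No figure in the protocol is in dispute on this point, so the main check is to set the statements side by side. A short calculation then shows what small ascertainment differences could do.

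**1. Can the statements coexist?**
- Who is blinded: everyone collecting follow-up data (3.1, 3.2, 8.3 and the day 90 text in 5.3).
- Who conducts follow-up: the central team, described in 8.3 as the blinded assessors. No separate unblinded caller is named.
- What they collect: VTE in both arms, but stocking adverse events and stocking adherence in the control arm only, at three contacts out of three (5.3, Appendix 1).
- Protection described: none. The protocol sets no question order, no hidden form branching and no second caller.

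**2. Result by mode of contact**
- Assessor-administered (telephone): the arm is known at day 7, and so before the day 21 to 35 and day 90 VTE questions. The blinding statement fails.
- Self-completed (web, SMS, written): nobody asks the questions. Blinding could survive if the arm-specific items were sent automatically and the replies kept from the assessors. The protocol does not describe this, but nothing in it rules it out.

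Because the blinding statement covers all collectors of follow-up data, the telephone route alone contradicts it.

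**3. Which part of the primary outcome is exposed?** The scan at 21 to 35 days has its own protection in 3.2: stockings are removed beforehand and the participant is told not to disclose the arm. What remains exposed is DVT or symptomatic PE reported at a contact and not captured on the scan. Section 5.3 requests imaging verification of such reports. That limits false positives, but it does not prevent missed reports or uneven chasing of confirmation.

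**4. Illustration of size (assumed shifts, not estimates)**

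Inputs: control rate 8%, margin 2 points and 8,264 participants before the allowance for missing outcomes (6.1); final threshold z = 2.00 (6.4).

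Check of the design first: n per arm = (1.960 + 1.282)² × 2 × 0.08 × 0.92 / 0.02² ≈ 3,867, or 7,734 in total, against the stated 7,736. It reproduces to rounding. The group-sequential total gives 8,264 / 2 = 4,132 per arm.

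Suppose the true rates are 8% and 10%, so that the excess equals the margin, and that a share b of EDPTP-alone participants have an event that goes unrecorded. Treating the final analysis as a single look:

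SE = √[(0.08 × 0.92 + p(1 − p)) / 4,132], with p = 0.10 − b

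P(false non-inferiority) = Φ(b / SE − 2.00)

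| b (points) | Events lost | SE (points) | P(false claim) |
|---|---|---|---|
| 0 | 0 | 0.629 | 2.3% |
| 0.1 | about 4 | 0.628 | Φ(−1.84) = 3.3% |
| 0.25 | about 10 | 0.625 | Φ(−1.60) = 5.5% |
| 0.5 | about 21 | 0.621 | Φ(−1.20) = about 12% |

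The opposite direction is just as possible. If there were no true difference and 0.25 points of extra events were recorded in the EDPTP-alone arm, SE = √[(0.08 × 0.92 + 0.0825 × 0.9175) / 4,132] = 0.601 points. The chance of showing non-inferiority would then be Φ((2 − 0.25) / 0.601 − 2.00) = 82%, against Φ(2 / 0.597 − 2.00) = 91% without the shift.

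**The case against.** The strongest reply is that the exposed part of the endpoint may be small and hard to influence. The VTE question is close to factual, since it asks whether a diagnosis has been made. The endpoint requires imaging. Participants are told to attend the emergency department if they suspect a clot and not to wait for the study team (5.2), so diagnosis does not depend on the caller. The scan is timed to the stated three-week peak, and its operators' blinding is protected. All of this stands and limits the consequence. It does not make the blinding statement true for assessor-administered contacts.

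A reader might go further than the documents allow in three ways.

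- That every follow-up contact unblinds the assessor. This is strict only for contacts the assessor administers. Self-completed modes are permitted, and the share using each mode is not stated.
- That about 5% of participants have VTE exposed to this problem, taking the symptomatic rates of 4.8% and 5.5% in the single trial cited in section 1.2, and that a given relative difference in eliciting it inflates false claims by a known amount. Symptomatic DVT that the scan also captures is not exposed, section 6.1 puts PE at only 0.05–0.11%, and the protocol gives neither a split nor any basis for a differential.
- That the bias must favour non-inferiority. A caller uneasy about omitting stockings might probe the EDPTP-alone arm harder, which would work against it.

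**Conclusion.** The contradiction is real and needs correcting. For contacts an assessor administers, those collecting follow-up data cannot be blinded as stated, and the assessor-blinded label in the Study Summary's trial design line does not hold for VTE reported at those contacts and not captured on the scan. It does hold for the scan.

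The amount of bias cannot be calculated from the protocol, and neither can its direction. The 3.3% to 12% range shows only that losing roughly 4 to 21 events among 4,132 would matter at this margin. It rests on an 8% control rate, a true excess equal to the margin, a single look at z = 2.00 and losses confined to the EDPTP-alone arm. It should not be quoted as an expected error rate.

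**What to change.** In section 5.3 and Appendix 1:

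- Have assessors ask the VTE items first and lock them in REDCap before anything else is recorded.
- Collect stocking adverse events and stocking adherence through the existing participant-completed web, SMS or written route, sent automatically, with the replies hidden from the blinded assessors.

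Both parts are needed. Asking VTE first protects only the contact in progress: an assessor who hears the stocking answers at day 7 knows the arm at the later contacts.

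For participants who can be reached only by telephone, or if the change is not made, restrict the blinding claim to the scan operators. That means the Study Summary design line, sections 3.1 and 3.2, the day 90 text in 5.3, and 8.3. Contact-reported VTE should then be reported as collected unblinded.

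The cost is a reordered case report form, a restricted REDCap view, an automated message and a wording amendment. The downside is less telephone collection of adherence than the patient representatives preferred. Having allocation-aware site staff make the stocking calls instead is possible but may need extra resources.

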### **5.1.3. CONTROL**

Participants randomised to the control arm will receive both EDPTP post discharge and GCS for a period of time as per locally policy which may vary between Trusts.

GCS are elastic stockings worn on the lower limbs, often referred to by one of the brand names ThromboEmbolic Deterrent (TED®) stockings. They provide low pressure compression with the intended benefit to reduce the risk of VTE. Either below-knee or above-knee compression stockings may be used. The duration of stocking use should be as per local policy for example, until ambulant, discharge or post discharge.

The range of EDPTP available for the EDPTP and GCS stockings (the control group) will be the same as for the EDPTP alone group. As above agents commonly used include LMWH e.g., Tinzaparin, Enoxaparin, or DOACs e.g., Rivaroxaban, Apixaban. Prophylactic-dose thromboprophylaxis is prescribed at a lower dose in comparison to clinical indications for therapeutic anticoagulation, such as in the treatment of diagnosed DVT or PE. Extended duration pharmacological thromboprophylaxis is the practice of prescribing the thromboprophylaxis for a duration after hospital discharge. Prevention of DVT is a licenced indication for several LMWH and DOACs and recommended by NICE guidelines [NG89]. Aspirin is an antiplatelet medication that reduces platelet function with a variety of clinical indications. The use of aspirin as DVT prophylaxis in orthopaedic surgery is also recommended by NICE [NG89](17).

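### Section 3.2 calls the scan operator blinded in both arms, but its only non-disclosure instruction covers GCS-arm participants still wearing stockings at the scan

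*Protocol*

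**What the plan says.** Section 3.1 makes the trial open to those treated and those treating: "Clinicians and participants will be aware of their treatment allocation". Section 3.2 then sets out who is blinded, with no restriction by arm: "Assessors, being those who perform the lower limb DVT scan and those responsible for collecting follow-up data, will be blinded to the treatment allocation".

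The next sentence of 3.2 is the only one that says how scan blinding is to be kept. It opens with a condition, "If patients in the GCS arm are still wearing stockings at the time of the scan", and continues: "they will be instructed to remove them prior to entering the scan room and not inform the scanner of their treatment allocation". Both instructions, removal and silence, depend on that condition.

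Section 5.1.3 leaves the wearing period to sites: "The duration of stocking use should be as per local policy for example, until ambulant, discharge or post discharge". Section 5.3 schedules one screening scan for everyone: "Participants will undergo a bilateral full lower limb (groin to ankle) deep venous thrombosis scan at 21- 35 days post-intervention". The primary outcome in section 2.1 is "imaging-confirmed lower limb DVT with or without symptoms, or PE with symptoms, occurring up to 90 days post-surgery", so a symptomless DVT found by that scan counts in full.

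**The concern.** Because participants know their arm, the operator's blinding depends on what each participant says or shows. The stated safeguard leaves out two groups:

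- everyone allocated to EDPTP alone, which is half of a 1:1 trial;
- GCS participants whose stocking use has ended by days 21-35, which section 5.1.3 allows.

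Neither group is asked to keep quiet. The blinding claim covers both arms, but the procedure behind it reaches only part of one.

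An operator who learns the arm may search more or less carefully, or call an equivocal vein differently. The protocol describes no independent re-reading of the scans, so such a shift would pass into a comparison judged against a 2-point margin. The trial would still be reported as assessor-blinded.

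**Working it through.** **1. Who is covered, by the wording**

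| Group at the day 21-35 scan | Knows allocation (3.1) | Operator said to be blinded (3.2) | Told not to disclose (3.2) |
|---|---|---|---|
| GCS arm, still in stockings | yes | yes | yes |
| GCS arm, stockings already stopped | yes | yes | not stated |
| EDPTP alone | yes | yes | not stated |

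Section 5.3, its day 21-35 subsection and Appendix 1 add no concealment instruction.

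**2. The plan's sample size, reproduced**

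Inputs from section 6.1: 8% in both arms, margin 2 points, one-sided 2.5%, 90% power.

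n per arm = (1.960 + 1.282)² × 2 × 0.08 × 0.92 / 0.02² ≈ 3,867, so 7,734 in total against 7,736 stated. The group sequential total is 8,264, or 4,132 per arm, and 8,264 / 0.96 ≈ 8,608 as stated. The 4,132 per arm is used below.

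**3. Rough share of events found only by the scan**

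The protocol gives no such share. Section 1.2 reports symptomatic-only VTE rates of 4.8% and 5.5% in the one direct trial; section 6.1 plans on 8%.

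- 1 − 5.5/8 = 31%
- 1 − 4.8/8 = 40%

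Against the pooled DVT rates the same step gives 25-35% (7.37%, EDPTP plus GCS) and 50-56% (10.97%, EDPTP alone). The rates come from different studies, so this is only a guide to scale.

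**4. Illustration: under-detection in the EDPTP-alone arm**

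Assume true rates of 8% (control) and 10% (EDPTP alone), exactly at the margin. Let s be the scan-only share and m the fraction of scan-only events missed in the EDPTP-alone arm.

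- Observed rate p = 0.10 × (1 − s·m); observed difference d = p − 0.08
- SE = √[p(1 − p)/4,132 + 0.08 × 0.92/4,132]
- P(declare non-inferiority) = Φ((0.02 − d)/SE − 1.96)

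| s | m | p | d | SE | P(false non-inferiority) |
|---|---|---|---|---|---|
| any | 0 | 10.00% | 2.00 points | – | 2.5% |
| 31% | 5% | 9.845% | 1.845 | 0.00627 | 4.3% |
| 31% | 10% | 9.69% | 1.69 | 0.00624 | 7.2% |
| 40% | 5% | 9.80% | 1.80 | 0.00626 | 5.0% |
| 40% | 10% | 9.60% | 1.60 | 0.00623 | 9.4% |

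**5. The other direction: over-detection in the EDPTP-alone arm**

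With both true rates at 8%, the observed EDPTP-alone rate becomes 0.08 × (1 + s·m). Power without any shift is 92%.

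| s | m | Observed EDPTP-alone rate | Power |
|---|---|---|---|
| 31% | 5% | 8.124% | 88% |
| 31% | 10% | 8.248% | 83% |
| 40% | 5% | 8.16% | 87% |
| 40% | 10% | 8.32% | 80% |

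With true rates at the margin, the same over-detection lowers false non-inferiority to about 0.5-1.4%.

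Both illustrations use a fixed design with a critical value of 1.96. The final threshold of 2.00 in section 6.4 would lower the probabilities slightly.

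**The case against.** The best defence is that 3.2 blinds scan operators without condition, so the intent covers both arms. Stockings are a visible clue in one arm only, so a measure against that clue has to be one-armed. And because wearing may end at ambulation or discharge, bare legs at days 21-35 do not reveal the arm. All of this stands as far as the visible clue goes. It does not answer spoken disclosure, which is possible in both arms and which 3.2 addresses only for those still in stockings.

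A second defence is that participant information, appointment wording and scan instructions are not shown and may already tell everyone to stay silent. That also stands: the point is about what the protocol states, not about what participants will in fact be told.

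Four stronger readings are tempting, and the documents do not support them:

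- **Stockings come off only at the scan-room door, leaving marks on the legs.** Section 3.2 requires removal before entry. It does not say where, how long before, or when the instruction is given. Visible marks are conjecture.
- **The scan supplies most primary events.** No section says so. At the planned 8% rate the protocol's figures point to 31-40%; only the pooled EDPTP-alone rate reaches one half.
- **A 5% or 10% shortfall raises false non-inferiority to 12% or 37%.** Those figures arise only if the shortfall applies to every primary event. Symptomatic DVT or PE diagnosed outside the screening scan is not exposed to this operator's judgement.
- **The bias would favour EDPTP alone.** An operator who thinks that going without stockings is riskier might look harder. Neither direction has evidence in the protocol.

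**Conclusion.** The point holds as a gap in procedure, not in intent. Section 3.2 promises operator blinding in both arms and fixes a non-disclosure step that reaches only GCS-arm participants still in stockings. This is more than detail left to another document, because the protocol states the step and states it too narrowly.

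The possible effect is moderate. If 31-40% of events are scan-only and 5-10% of those are missed in the EDPTP-alone arm, false non-inferiority at the margin is about 4-9% rather than 2.5%. Over-detection of the same size in that arm would cut power from 92% to about 80-88%. The scan-only share is a rough cross-study figure, and the detection shift is purely an assumption; it may be nil. The case for acting is that the remedy costs almost nothing and that blinding lost at a scan cannot be restored.

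**What to change.** Reword section 3.2 so that all participants in both arms are told, before the scan visit, not to disclose their allocation to the scan operator. Keep the existing requirement that anyone still in stockings removes them before entering the scan room. If participant or appointment materials already give this instruction to everyone, the protocol should say so.

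Optionally, add one item to the scan form recording whether the operator became aware of the allocation, and report it descriptively by arm. Any analysis that leaves out such scans should be labelled exploratory: it is a post-randomisation exclusion that may differ between arms, and the item is completed by someone who may already know the finding.

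The cost is one protocol sentence, one line in the appointment message and, if wanted, one form item. The sample size, margin and stopping boundaries do not change.
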